# The FEED1 trial: protocol for a randomised controlled trial of full milk feeds versus intravenous fluids with gradual feeding for preterm infants (30–33 weeks gestational age)

**DOI:** 10.1186/s13063-021-05994-z

**Published:** 2022-01-20

**Keywords:** Clinical trial, Protocol, Preterm infant, Feeding, Neonatal, Full milk, Enteral feeding

## Abstract

**Background:**

In the UK, approximately 8% of live births are preterm (before 37 weeks gestation), more than 90% of whom are born between 30 and 36 weeks, forming the largest proportion of a neonatal units’ workload. Neonatologists are cautious in initiating full milk feeds for preterm infants due to fears of necrotising enterocolitis (NEC). There is now evidence to dispute this fear. Small studies have shown that feeding preterm infants full milk feeds enterally from birth could result in a shorter length of hospital stay, which is important to parents, clinicians and NHS services without increasing the risk of NEC. This trial aims to investigate whether full milk feeds initiated in the first 24 h after birth reduces the length of hospital stay in comparison to introduction of gradual milk feeding with IV fluids or parenteral nutrition.

**Methods:**

FEED1 is a multi-centre, open, parallel group, randomised, controlled superiority trial of full milk feeds initiated on the day of birth versus gradual milk feeds for infants born at 30^+0^ to 32^+6^ (inclusive) weeks gestation. Recruitment will take place in around 40 UK neonatal units. Mothers will be randomised 1:1 to full milk feeds, starting at 60 ml/kg day, or gradual feeds, as per usual local practice. Mother’s expressed breast milk will always be the first choice of milk, though will likely be supplemented with formula or donor breast milk in the first few days. Feeding data will be collected until full milk feeds are achieved (≥ 140 ml/kg/day for 3 consecutive days). The primary outcome is length of infant hospital stay. Additional data will be collected 6 weeks post-discharge. Follow-up at 2 years (corrected gestational age) is planned. The sample size is 2088 infants to detect a between group difference in length of stay of 2 days. Accounting for multiple births, this requires 1700 women to be recruited. Primary analysis will compare the length of hospital stay between groups, adjusting for minimisation variables and accounting for multiple births.

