### Sample size and recruitment

Our sample size calculation has been based upon detecting a between group difference in means of length of stay of 2 days. Input from our parent representatives suggests that from a family perspective even a short reduction in length of hospital stay could make a huge difference to parents. In addition, from a cost-saving perspective, a reduction in length of stay of 2 days for this population of infants could result in £5.6 m annual savings for the NHS in England and Wales and > 12,000 days of increased neonatal cot capacity.

Data from audits and previous studies suggest that the distribution of length of hospital stay in this population is approximately normal. To detect a difference in means of 2 days between the two groups with 90% power, 1:1 allocation and 5% two-sided significance requires 1778 infants, assuming a standard deviation of 13 [23, 24]. Allowing for 2% non-collection of the primary outcome data due to death, no consent for data collection after oral assent and infants remaining in hospital at the end of data collection and accounting for clustering will require 2088 infants and recruitment of approximately 1770 women. The inflation to account for clustering assumes that 15% and 1.4% of pregnancies will be twin and triplets respectively and that the intracluster correlation coefficient for length of hospital stay for infants from the same pregnancy is 0.82 [4].

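### The abstract asks for 1700 women to yield 2088 infants; the sample-size section asks for about 1770, and only 1770 follows from the stated multiple-birth rates

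*Protocol article*

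**What the plan says.** The abstract (Methods paragraph) gives the target in infants first: "The sample size is 2088 infants to detect a between group difference in length of stay of 2 days". It then converts infants to women: "Accounting for multiple births, this requires 1700 women to be recruited".

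The section Sample size and recruitment sets out the derivation. Before any inflation: "To detect a difference in means of 2 days between the two groups with 90% power, 1:1 allocation and 5% two-sided significance requires 1778 infants". The SD behind this figure is 13 days. The inflation starts from "Allowing for 2% non-collection of the primary outcome data due to death" and other causes, adds clustering of siblings, and "will require 2088 infants and recruitment of approximately 1770 women". The clustering step "assumes that 15% and 1.4% of pregnancies will be twin and triplets respectively", with an intracluster correlation of 0.82 between infants of the same pregnancy.

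The section Randomisation and blinding makes the mother the unit of randomisation. The section Trial status expects recruitment to run until September 2022 at the earliest; the article appeared in January 2022.

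**The concern.** The two places agree on the infant target and on the 2-day difference. They differ only in the number of women, by 70. Rounding does not explain this, because 1770 to the nearest hundred is 1800.

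The number of women matters for two reasons. Women are what sites recruit and randomise. And with an intracluster correlation of 0.82 a second or third sibling adds little information, so power depends mainly on the number of women. The abstract is also the part most readers will consult, and the target was still live when it was published.

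**Working it through.** **Inputs**, all from Sample size and recruitment: difference 2 days, SD 13, two-sided 5%, power 90%, 1:1 allocation, 2% loss, 15% twin and 1.4% triplet pregnancies (so 83.6% singleton), intracluster correlation 0.82. The documents do not state which design-effect formula was used, so I show more than one.

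**1. Infants before inflation.** Per arm, n = 2 × (1.960 + 1.282)² × 13² / 2² = 888, total 1776. The t-test version gives 1777.7, that is 1778. The stated 1778 reproduces.

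**2. Infants per woman.** 0.836 × 1 + 0.15 × 2 + 0.014 × 3 = 0.836 + 0.300 + 0.042 = 1.178.

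**3. Infants after inflation**, 1778 × design effect / 0.98:

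- Mean cluster size: 1 + 0.178 × 0.82 = 1.146, giving 2079 infants, or 1765 women.
- Mixed-model weighting: effective infants per woman = 0.836 + 0.300/1.82 + 0.042/2.64 = 1.0167. The design effect is 1.178/1.0167 = 1.159, giving 2102 infants, or 1784 women.
- Implied by 2088 itself: 2088 × 0.98 / 1778 = 1.151.
- Size-weighted: 1.267, giving 2299 infants. This does not reproduce 2088, so I take it that it was not the method used.

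The first two bracket the stated 2088, and both put the number of women close to 1770.

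**4. Women for 2088 infants.** 2088 / 1.178 = about 1772. The stated figure of approximately 1770 reproduces (1770 × 1.178 = 2085 infants).

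**5. The abstract's figure.** 1700 × 1.178 = 2003 infants. The shortfall is 2088 − 2003 = 85, or 4.1%. To reach 2088 from 1700 women would take 2088 / 1700 = 1.228 infants per woman, against the assumed 1.178. Reading 15% and 1.4% as shares of infants instead of pregnancies does not help: 2088 × (0.836 + 0.15/2 + 0.014/3) = about 1912 women, which is further from 1700.

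**6. Power if recruitment ended at each figure.** Effective N = infants × 0.98 / design effect; power = Φ((2/13) × √N / 2 − 1.960).

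| Design effect | 1700 women | 1770 women |
|---|---|---|
| 1.146 (mean size) | 88.9% | 90.1% |
| 1.151 (implied by 2088) | 88.8% | 90.0% |
| 1.159 (mixed model) | 88.6% | 89.8% |

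Within each row the difference is about 1.2 points. Measured against the nominal 90%, 1700 women fall 1.1 to 1.4 points short.

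**The case against.** The strongest reply is that this is a slip in an abstract with no consequence. The abstract names 2088 infants as the sample size and only derives the number of women from it. The full derivation in the body is coherent and gives about 1770. A mistyped digit is the likeliest explanation.

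Most of that stands. A reader might infer that the trial will stop at 1700 women and so lose its 90% power. The documents do not support this: no section makes 1700 a stopping rule, and nothing shows that anyone recruited to it. Even if it were used, the loss would be little more than one percentage point. Nor does the 90% line separate the two figures cleanly. With mixed-model weighting, 1770 women also fall marginally below it, at 89.8%, and that weighting is my choice, not one the article states.

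A reader might also conclude that recruitment should close only when a count of women and a count of infants have both been met. Correcting the figure does not call for such a rule, and it could enrol more participants than planned whenever the multiple-birth rate departs from the assumed one.

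What does not stand is the suggestion that the figure can be left alone. It is a wrong number printed in this article and contradicted by the article's own derivation. It is not a detail that the full protocol or the analysis plan would be expected to supply.

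**Conclusion.** The abstract's 1700 women is wrong as written. Under the stated twin and triplet rates, 2088 infants correspond to about 1772 women, which confirms the figure in the sample-size section. The point rests on that inconsistency and on the gap of 85 infants (4.1%), not on a material loss of power.

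The effect on power, about 88.6% to 88.9% against about 90%, is slight and arises only if 1700 women were used as the recruitment target. These power figures assume the protocol's SD, loss rate, multiple-birth rates and intracluster correlation, and a design effect between 1.146 and 1.159. The conclusion that 1700 does not yield 2088 infants needs only the multiple-birth rates.

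**What to change.** In the abstract, change 1700 to approximately 1770 women. If 1700 is really the intended number, say so in both places and restate what it delivers under the stated assumptions: about 2003 infants and just under 89% power.

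The cost is one corrected figure. It adds no participants to the target already given in the sample-size section, and it needs no new rule for when recruitment is complete.

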**Discussion:**

This trial will provide high-quality evidence on feeding practices for preterm infants. Full milk feeds from day of birth could result in infants being discharged sooner.

**Trial registration:**

ISRCTN ISRCTN89654042. Prospectively registered on 23 September 2019: ISRCTN is a primary registry of the WHO ICTRP network, and all items from the WHO Trial Registration dataset are included.

## Background

In preterm infants, early establishment of enteral feeding is associated with reduced sepsis, improved growth [1] and enhanced neurodevelopment [2]. Achieving full milk feeds sooner and improving growth without infection or necrotising enterocolitis (NEC) may help the infant be ready for home earlier, reducing the length of hospital stay. Despite evidence to the contrary [3], clinicians often delay initiating feeds or increment feeds slowly due to fear of NEC. The recently completed Speed of Increasing milk Feeds Trial (SIFT) provides firm evidence from over 2800 infants that faster advancement of milk feeds does not increase the risk of NEC even in the most premature infants [4]. In this large, multi-centre trial comparing fast (30 ml/kg/day) vs. slow (18 ml/kg/day) feed increments in 2804 infants born before 32 weeks gestation, the risks of NEC or death were not increased by the faster increment in feeds. Faster fed infants achieved full feeds quicker and received intravenous (IV) fluids for fewer days. A recent Cochrane review assessing advancement of feed volumes in preterm infants concluded that slow advancement of enteral feed volumes results in several days of delay in establishing full milk feeds and may increase the risk of invasive infection [1] possibly due to increased iatrogenic infections from a longer duration of IV line placement.

These results indicate that there may be benefit from a faster approach to feeding. In infants between 30^+0^ to 32^+6^ weeks this could be achieved by providing their full fluid requirements solely as enteral feeds from day of birth without using IV fluids or parenteral nutrition, i.e. “full milk” feeds from the day of birth. A Cochrane review on early full enteral feeding in preterm infants included 6 randomised controlled trials involving 601 stable infants weighing between 1000 and 1500 g at birth [5]. A meta-analysis of length of hospital stay (4 studies, 398 infants) showed a mean difference of − 2.26 days in infants given early full enteral feeds. There was no difference in incidence of NEC. However, all studies were conducted in India and had a moderate to high risk of bias in several areas when assessed for methodological rigour. One small study included in the review included 46 infants (birth weight 1200–1500 g; mean gestation 31 weeks) who were randomised to receive full milk from one hour after birth or IV fluids and slow feed increments (20 ml/kg/d) [6]. They found that infants randomised to full milk feeding regained birth weight quicker, had improved growth at discharge, shorter duration of hospital stay and fewer cases of sepsis without an increased risk of NEC. Additionally, in a trial of 180 infants, Nangia et al. showed a mean difference of − 3.6 days in time taken to reach full enteral feeds in infants fed early enteral feeds and a reduction of 4.1 days in length of hospital stay [7]. These findings suggest it is potentially safe and may be better to start full milk feeds on the day of birth without increasing the risk of NEC and possibly reducing the risk of sepsis. An observational study also showed that implementing full milk feeds from birth is feasible and acceptable, with the infants receiving full enteral milk feeds having significantly fewer cases of NEC and sepsis, less antibiotics, less parenteral nutrition and a shorter average hospital stay [8]. These studies were all conducted in India where the preterm population, healthcare resources, infrastructure and delivery systems as well as treatments and risk factors are different to that in the UK. There have been no studies in the UK or other similar high resource settings investigating the strategy of feeding preterm infants “full milk” feeds from day of birth.

### Justification for study population

In 2018, in England and Wales, there were 656,925 live births of which 51,864 (7.9%) were preterm (born before 37 completed weeks gestation) [9]. Providing optimal nutrition is a cornerstone of neonatal care and the subject of many recent research studies including SIFT [4], ADEPT [10], NEON [11] and SCAMP [12]. These and other similar studies focus on extremely preterm infants (born before 30 weeks) at highest risk of adverse outcomes (death or NEC). However, more than 90% of preterm infants are born at or after 30 weeks, including the 12% of preterm infants who are eligible for FEED1. More mature preterm infants (≥ 34 weeks) typically do not require special care. Infants born at 30, 31 or 32 weeks comprise over 40% of preterm infants routinely admitted to neonatal units (in 2018 there were 5879 infants in this group in England and Wales) and form the largest proportion of workload for neonatal services. Treatments that reduce length of stay in this group of preterm infants could therefore impact the largest number of infants in neonatal units and their families.

### Justification for comparators

Infants that are fully milk fed need less monitoring and could be moved to lower dependency care. Adequate enteral nutrition could promote weight gain and reduce the risk of infections, potentially making infants ready for home sooner and reducing the length of hospital stay. This would make scarce higher dependency cots for sicker infants more readily available and avoid transferring infants further afield to access resources.

Strategies that aim to safely achieve a shorter hospital stay could improve care for all infants who require neonatal care. Full milk feeds may also reduce the cost of care by decreasing use of parenteral nutrition and IV fluids and reducing iatrogenic infections. Preterm birth is associated with long-term morbidities and large lifetime financial costs, placing strain on NHS finances and social care resources. Full milk feeds may improve nutrition and reduce morbidities such as sepsis, thereby improving neurodevelopmental outcomes and lifelong quality of life for this large group of infants. Such an approach that improves the care of preterm infants whilst simultaneously reducing the cost of care would achieve the NHS “Five Year Forward View” aim of achieving efficiency savings whilst maintaining and improving quality of care and safety [13]. There are also potential benefits for mothers and families from a less medical model of care, with opportunities for involvement in care, shorter mother-infant separation and improved satisfaction and mental health outcomes.

The FEED1 Trial addresses three of the top six research priorities identified by the James Lind Alliance [14]:
“What is the optimum milk feeding strategy and guidance (including quantity and speed of feeding and use of donor and formula milk) for the best long-term outcomes of premature infants?How can infection in preterm infants be better prevented?Which interventions are most effective to prevent necrotising enterocolitis in premature infants?”

This paper is reported in accordance with the Standard Protocol Items: Recommendations for Interventional trials (SPIRIT) guidelines [15].

### Objectives

To determine whether, in infants born at 30^+0^ to 32^+6^ weeks gestation, full milk feeds initiated in the first 24 h after birth reduces the length of infant hospital stay in comparison to IV fluids or parenteral nutrition with gradual milk feeding.

## Methods/design

This is a multi-centre, open, parallel group, randomised (1:1) controlled superiority trial of full milk feeds versus gradual milk feeds. Mothers and infants will be recruited from around 40 neonatal units in the UK. A list of participating sites can be found at www.feed1.ac.uk. The full protocol and other trial documentation, including participant information sheets and consent forms, can also be found on the trial website. An embedded Study Within a Trial (SWAT) is also included which is investigating methods of training sites. Details of the SWAT can be found on the SWAT repository [16, 17] and will be reported separately.

### Eligibility

Inclusion criteria include (i) infants born at 30^+0^ to 32^+6^ weeks gestation (inclusive) and ii) infants < 3 h (180 min) old (since recorded time of birth). Infants requiring respiratory support (such as via continuous positive airway pressure) or other supportive treatments will be included in the study if the clinician is in equipoise about the infant being randomised to either the “full milk” or the “gradual milk” arm. Similarly, well infants should only be included if the attending clinician is in equipoise about the best feeding regime and the infant being randomised to either “full milk” or “gradual milk” groups. Exclusion criteria include (i) infants with known congenital abnormalities of the gastrointestinal tract or other congenital conditions that make enteral feeding unsafe, (ii) infants who are small for gestational age (SGA) (birth weight < 10^th^ centile) and have evidence of reversed end-diastolic flow on antenatal umbilical artery Doppler ultrasound and (iii) mothers who have participated in the trial during a previous pregnancy.

### Interventions

For infants in the full milk group (intervention), fluids will be started as milk at 60 ml/kg/day, increased as per their individual requirements and in line with standard neonatal practice. The choice of feeding intervals will be determined by local policy and clinician’s preference. Wherever possible, mother’s expressed breast milk will always be the first preference for infant milk feeds. It is likely that mother’s breast milk will need to be supplemented with additional milk, i.e. either infant formula milk or donor breast milk in the first few days. The decision as to the type of milk used will be made by the mother and the site, in line with the site’s local policy. For infants in the gradual milk group (control), fluids will be given in accordance with standard practice at the site. This may include milk feeds, starting at a maximum of 30 ml/kg/day on day 1 with a minimum of 30 ml/kg/day of supplementary IV fluids or parenteral nutrition. Adherence to the randomised allocation will be monitored on a regular basis by the Trial Management Group. Due to the pragmatic nature of this neonatal feeding trial, there are no prohibited interventions or concomitant medications.

### Outcomes

The primary outcome is length of infant hospital stay. Since hospitals could apply different discharge criteria, a secondary outcome of time until objective discharge criteria are met has also been included. The statistician, blinded to treatment allocation, will use the date at which each infant first met all three of the following criteria: (i) current weight ≥ 1700 g, (ii) infant is able to take at least one full suck feed assessed as adequate and (iii) infant has been off additional temperature support for ≥ 24 h. Daily data will be collected to determine the day on which the infant achieved all the three features to determine the time until objective discharge criteria are met. The primary and all secondary outcomes, including the five elements (domain, specific measurement, specific metric, method of aggregation and time point) as defined by Saldanha et al [18], are listed in Table 1.

**Table 1 Tab1:** Primary and secondary outcome measures

Domain	Specific measurement	Specific metrics	Method of aggregation	Time point
**Primary outcome**				
Length of hospital stay	Date of hospital discharge	Difference between the date the infant is discharged and date of randomisation	Mean and standard deviation (SD), per group	Hospital discharge
**Secondary outcomes**				
Survival	Date of death as recorded on eCRF. Date of death as recorded on eCRF	Death between date of randomisation and date of hospital discharge. Death between date of randomisation and 6 weeks corrected gestational age	Proportion of infants alive, per group. Proportion of infants alive, per group	Hospital discharge 6 weeks corrected gestational age
Microbiologically confirmed (positive blood/cerebrospinal fluid culture) or clinically suspected late-onset sepsis	Presence of confirmed or suspected late-onset sepsis on microbiology report and recorded in eCRF^1^	Microbiologically confirmed late-onset sepsis between date of randomisation and hospital discharge	Proportion of infants with microbiologically confirmed late-onset sepsis, per group	Hospital discharge
Necrotising enterocolitis (NEC) (Bell’s stage 2 or 3) [19]	Presence of NEC (stage 2 or 3) recorded on eCRF^1^	Diagnosis of NEC (stage 2 or 3) between date of randomisation and hospital discharge	Proportion of infants with NEC (stage 2 or 3), per group	Hospital discharge
Time taken to maintain full milk feeding	Full milk feeds reached, defined as at least 140 ml/kg/day for three consecutive days^2,^ as recorded on eCRF	Derived from the date the infant achieves full feeds, recorded on CRF, and date of randomisation	Mean (and SD) and/or median (and IQR), per group	During hospital admission, in accordance with criteria for reaching full milk feeds
Time to regain birth weight	Birth weight regained, as recorded on eCRF	Derived from the date the infant regains birth weight and date of randomisation	Mean (and SD) and/or median (and IQR), per group	During hospital admission
Growth of infant	Growth *Z* scores (length, weight and head circumference), corrected for gestational age as per UK-NICM growth charts [20]	Derived from growth *Z* scores, expected date of delivery and infant sex	Mean (and SD) and/or median (and IQR), per group	Hospital discharge
Breast-feeding	Infant being breast-fed, as recorded on CRF. Infant being breast-fed, as recorded on 6-week parent-completed questionnaire	Infant being breast-fed at time of hospital discharge. Infant being breast-fed at 6 weeks (corrected gestational age)	Proportion of infants breast-feeding, per group. Proportion of infants breast-feeding, per group	Hospital discharge. 6 weeks corrected gestational age
Breast milk feeds	Infant being fed mother’s breast milk, as recorded on eCRF. Infant being fed mother’s breast milk, as recorded on 6-week parent-completed questionnaire	Infant being fed mother’s breast milk at time of hospital discharge. Infant being breast fed mother’s breast milk at 6 weeks (corrected gestational age)	Proportion of infants being fed mother’s breast milk, per group. Proportion of infants being fed mother’s breast milk, per group	Hospital discharge. 6 weeks, corrected gestational age
Number of days of cannulae	Number of days of peripheral cannula and IV cannulae inserted, as recorded on eCRF	Number of days of peripheral cannula and IV cannulae inserted, until infant reaches full milk feeds	Mean (and SD) and/or median (and IQR), per group	Date infant reaches full milk feeds, whilst in hospital
Number of days of infant receiving parenteral nutrition	Number of days of infant receiving parenteral nutrition, as recorded on eCRF	Number of days of infant receiving parenteral nutrition until hospital discharge	Mean (and SD) and/or median (and IQR), per group	Hospital discharge
Number of central venous lines inserted	Number of central venous lines, including umbilical and percutaneous or surgically inserted venous lines), as recorded on eCRF	Number of central venous lines between date of randomisation and date of hospital discharge	Mean (and SD) and/or median (and IQR), per group	Hospital discharge
Number of central line days	Number of days infant has a central line, as recorded on eCRF	Number of central line days between date of randomisation and date of hospital discharge	Mean (and SD) and/or Median (and IQR), per group	Hospital discharge
Time until objective discharge criteria are met	Objective discharge criteria, as recorded on eCRF	Derived from the date the objective discharge criteria is met and date of randomisation	Mean (and SD) and/or median (and IQR), per group	During hospital admission
Length of neonatal unit stay	Length of stay in (i) neonatal intensive care, (ii) high dependency care, (iii) special care, (iv) translational care, as recorded on eCRF	Derived from days spent in each type of neonatal unit between date of randomisation and date of discharge	Mean (and SD) and/or median (and IQR), per group	Hospital discharge
Retinopathy of prematurity (ROP)	Diagnosis of ROP, as recorded on eCRF	Diagnosis of ROP between date of randomisation and date of hospital discharge	Proportion of infants with ROP, per group	Hospital discharge
Chronic lung disease (CLD)	Diagnosis of CLD, as recorded on eCRF	Diagnosis of CLD between date of randomisation and date of hospital discharge	Proportion of infants who are mechanically ventilated or on nasal CPAP or in supplemental oxygen at 36 weeks corrected gestational age, per group	Hospital discharge
Brain injury	Diagnosis of intraventricular haemorrhage (grade 3 or 4), periventricular leukomalacia or hydrocephalus (requiring a shunt) on cranial ultrasound, recorded on eCRF	Diagnosis of brain injury (as per definitions) between date of randomisation and date of hospital discharge	Proportion of infants with recorded evidence of brain injury (grade 3 or 4 intraventricular haemorrhage, periventricular leukomalacia or hydrocephalous requiring shunt, per group	Hospital discharge
Blood glucose/hypoglycaemia	Number of blood glucose tests, as recorded on eCRF. Number of blood glucose tests indicating hypoglycaemia (< 2.2 mmol/L). Number of blood tests indicating severe hypoglycaemia (< 1.0 mmol/L)	Number of blood glucose tests, between date of randomisation and date of hospital discharge. Number of blood glucose tests < 2.2 mmol/L, between date of randomisation and date of hospital discharge. Number of blood glucose tests < 1.0 mmol/L between date of randomisation and date of hospital discharge	Mean (and SD) and/or median (and IQR), per group. Mean (and SD) and/or median (and IQR), per group. Mean (and SD) and/or median (and IQR), per group	Hospital discharge. Hospital discharge. Hospital discharge
Hospital visits	Number of hospital visits, including day care and overnight admissions, as recorded on 6-week parent-completed questionnaire	Number of hospital visits between date of hospital discharge and 6 weeks corrected gestational age	Mean (and SD) and/or median (and IQR), per group	6 weeks corrected gestational age
Parental satisfaction and wellbeing	Preterm birth experience and satisfaction scale (P-BESS) [21], completed by parents	P-BESS total score (and subscales for interpersonal care, information and explanations, lack of confidence in staff) at 6 weeks corrected gestational age	Mean (and SD) and/or median (and IQR), per group	6 weeks corrected gestational age

^1^Indeterminate cases will be subject to a blinded endpoint review to make a final determination

^2^Infants who are partially or exclusively breast fed will be considered to have achieved full enteral milk feeds if their intake of milk (breast feeding plus measured volume of additional milk) is considered equivalent to full enteral milk feeds

Outcome measures included have been guided by the Core Outcomes in Neonatology (COIN) core outcome set [22]. Discussions are ongoing to obtain separate funding to collect longer-term follow-up data at 2 years corrected gestational age. In addition, the research team are in discussions with researchers based in other countries, such as Canada and Australia, to set-up parallel studies. This will be to provide sufficient power to assess outcomes of NEC and sepsis; these outcomes occurred in 1% and 12% of infants retrospectively in the SIFT Trial among those who would have been eligible for FEED1.

